## 2.3 Data Acquisition

|                                                                                                    |
|----------------------------------------------------------------------------------------------------|
| Study design: Randomized controlled trial with parallel assignment                                 |
| Contact information for team member responsible for data collection / acquisition: [name] |
| Where dataset is stored: StanfordMed Box                                                           |

## 3. Outcomes, Exposures, and Additional Variables for Interest

### 3.1 Primary Outcome(s)

| Outcome | Description                         | Variables and source | Specifications                |
|---------|-------------------------------------|----------------------|-------------------------------|
| LDL     | Measured at baseline, 4 and 8 weeks |                      | Continuous, measured in mg/dL |

### 3.2 Secondary Outcome(s)

| Outcome         | Description                         | Variables and source | Specifications                      |
|-----------------|-------------------------------------|----------------------|-------------------------------------|
| HDL             | Measured at baseline, 4 and 8 weeks |                      | Continuous, measured in mg/dL       |
| Triglycerides   | Measured at baseline, 4 and 8 weeks |                      | Continuous, measured in mg/dL       |
| Fasting Insulin | Measured at baseline, 4 and 8 weeks |                      | Continuous, measured in $\mu$ IU/mL |
| Fasting Glucose | Measured at baseline, 4 and 8 weeks |                      | Continuous, measured in mg/dL       |
| TMAO            | Measured at baseline, 4 and 8 weeks |                      | Continuous, measured in $\mu$ M     |
| Weight          | Measured at baseline, 4 and 8 weeks |                      | Continuous, measured in kg          |

|            |                                     |  |                               |
|------------|-------------------------------------|--|-------------------------------|
| Serum B-12 | Measured at baseline, 4 and 8 weeks |  | Continuous, measured in pg/ml |
|------------|-------------------------------------|--|-------------------------------|

### 3.3 Exploratory Outcome(s)

| Outcome              | Description                         | Variables and source | Specifications                                                                                                                                                                                                                                                                            |
|----------------------|-------------------------------------|----------------------|-------------------------------------------------------------------------------------------------------------------------------------------------------------------------------------------------------------------------------------------------------------------------------------------|
| Inflammation Markers | Measured at baseline, 4 and 8 weeks |                      | Continuous                                                                                                                                                                                                                                                                                |
| Alpha Diversity      | Measured at baseline, 4 and 8 weeks |                      | Continuous, number of observed sequence variants ("species") determined by standard 16S rRNA amplicon sequencing (V3-V5 region followed by DADA2 to define error-corrected sequence variants).
Note: Higher alpha diversity is better. The units are the # of sequence variants |

## 4. Statistical Analysis Plan

Data management and data quality check:

For all variables (demographic and clinical variables), we will present spaghetti plots by arm. Visually we will examine the plots for any possible data errors (e.g., implausible value, implausible change between time points, etc.) or extreme outliers. Additionally, for all variables, we will present histograms, by arm, as well as, overall participants. Here, we will examine the distributions for skewness or multi-modality; and determine if any variable transformations are necessary for modeling. Lastly, we will present the available sample size for each variable at each time point, within a study arm.

### 4.1 Demographic and Clinical Characteristics ("Table 1")

*Demographic variables:* age (continuous), sex, race/ethnicity, twins housing arrangement (dichotomous: living together or separate)

*Clinical variables:* LDL-C, HDL-C, triglycerides, fasting insulin, fasting glucose, TMAO, weight, serum B12

*Process variables:* caloric intake, macronutrient intake

Mean (standard deviation) or n (percent) will be presented for continuous and categorical variables, respectively. Variables with skewed distributions will also be presented as median (interquartile range) -- present on second line or in text or remove mn(sd). Table 1 will present summary statistics, by arm. We will present absolute standardized differences (ASDs) by study arm to investigate if there are any small, medium, or large differences between arms (0.2, 0.5, or 0.8, respectively). Furthermore, given participants are identical twin pairs, we will present summary statistics for baseline variable differences within a twin pair. We note process variables will be used to examine diet adherence; participants on a vegan diet should have no animal protein and cholesterol and higher fiber intake (than baseline).

### 4.2 Analysis Plan for Aim 1

For the primary analysis, we want to investigate a difference in the change from baseline for LDL between a vegan and carnivorous diet after 8 weeks, among identical twins. The primary outcome will be absolute LDL. The primary analysis will include all available data. A linear mixed model will be used and include fixed effects for diet and time (baseline as reference) and an interaction effect for diet by time, and a random effect for twin pair, to account for the correlation between identical twins (i.e. random intercept allows intercept to vary for each twin pair). A Wald test will be used to evaluate a significant difference in diet at 8 weeks from baseline (interaction term), at a 5% significance level. If a significant difference at 8 weeks is observed, we will use a Wald test to evaluate a significant difference in diet at 4 weeks from baseline. Here, we want to determine if the improvement in LDL can be observed as soon as 4 weeks on a vegan diet. Finally, we will present model estimates (95% CI) for diet at 4 and 8 weeks.

We will implement the following secondary analyses. For each secondary outcome, we will evaluate a model similar to the primary model as described above. In Table 1, if any demographic, clinical, or process variables display more than small differences between arms (as measured by  $ASD > 0.2$ ), we will evaluate the primary model as described

above, while adjusting for the variable(s).

Lastly, we will consider the following exploratory analyses. For academic purposes, we will implement a conservative approach that ignores the correlation within twin pairs and perform a two-sample t-test for the primary and secondary outcomes. Additionally, we will implement an overly liberal approach that incorrectly assumes identical twins can represent the same experimental unit in a matched t-test.

We note 4 pairs of twins were selected for media representation on a Netflix show; subsequently, these participants were supervised more than other participants. In a sensitivity analysis, we will run the primary analyses, excluding these 4 pairs of twins.

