#### RANDOMIZATION

Participants will not be randomized until all baseline clinic visits, food logs, and online questionnaires are completed. One of the individuals in each pair of twins will be randomized to a vegan diet, and the other will be randomized to an omnivore diet.

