#### DATA COLLECTION

We will collect stool, blood (through venous blood draw at the CTRU), and blood microsamples using a Tasso device at home, food logs, psychosocial data, cognitive data, and physical activity data from all participants at the following time points:

Week -1

Week 0 (Baseline and time of randomization, CTRU)

Week 2

Week 4 (CTRU)

Week 6

Week 8 (end of intervention, CTRU)

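### The primary model gives baseline LDL a free diet effect although baseline precedes randomisation, so the week-8 estimate is an unadjusted difference in change and usually loses some precision

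*Combined protocol and SAP*

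**What the plan says.** SAP section 4.2 models LDL itself at baseline, week 4 and week 8 ("The primary outcome will be absolute LDL"). The model is to "include fixed effects for diet and time (baseline as reference) and an interaction effect for diet by time", with "a random effect for twin pair, to account for the correlation between identical twins" as the only random term. The primary test is stated as follows: "A Wald test will be used to evaluate a significant difference in diet at 8 weeks from baseline (interaction term"), "at a 5% significance level".

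The protocol's Study Procedures fix the order of events: "Participants will not be randomized until all baseline clinic visits, food logs, and online questionnaires are completed". The visit list agrees ("Week 0 (Baseline and time of randomization, CTRU")), and allocation is within pair ("One of the individuals in each pair of twins will be randomized to a vegan diet").

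The primary model contains no baseline adjustment. The SAP's only covariate adjustment is a secondary re-run of the primary model, adding any Table 1 variable whose absolute standardised difference (ASD) between arms exceeds 0.2. LDL-C is a Table 1 variable. Secondary outcomes use a similar model. The number of pairs is 22 in the SAP overview and 24 in protocol section 8(a).

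**The concern.** With baseline as the reference visit, the diet main effect is the difference between arms in mean baseline LDL. Both arms are measured before allocation, so that difference has expectation zero by design. Estimating it freely discards that knowledge. Whatever chance imbalance arises at baseline is subtracted in full from the week-8 difference, although only a fraction of it is expected to persist.

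What is at stake is precision. The trial has 22 to 24 pairs, the week-4 test is done only if week 8 is significant, and the same model form carries over to every secondary outcome, so any loss recurs throughout. The ASD rule may also give the impression that baseline LDL imbalance will be dealt with if it appears.

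**Working it through.** **Inputs.** From the documents: model form, test, visits, order of baseline and randomisation, and 22 pairs. Not in the documents: the SD of LDL, any correlation, an effect size or a power figure. There is therefore no stated figure to reproduce, and r is assumed over a range.

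**Notation.** D_t is the vegan-minus-omnivore LDL difference within a pair at visit t, with variance V at each visit; r = corr(D_0, D_8); n is the number of pairs; data are complete.

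**1. What the interaction estimates.** With complete data it equals mean(D_8) − mean(D_0). Fitting the SAP model to two simulated 22-pair data sets gave −1.428 and −10.543, identical to the difference in mean change in each.

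**2. Variances.**
- Change score: 2V(1 − r)/n.
- Adjusted for baseline, large sample: V(1 − r²)/n.
- Ratio: (1 − r²)/(2(1 − r)) = (1 + r)/2.
- ANCOVA on pair differences also pays for estimating its slope, a factor of about (n − 2)/(n − 3) = 20/19 ≈ 1.05 at 22 pairs.

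**3. Variance relative to a correctly specified change-score analysis.** The last two columns are simulated at 22 pairs, three visits, compound symmetry.

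| r (assumed) | (1 + r)/2 | Common-baseline model | ANCOVA on pair differences |
|---|---|---|---|
| 0.4 | 0.70 | 0.71 | 0.74 |
| 0.6 | 0.80 | 0.81 | 0.84 |
| 0.8 | 0.90 | 0.92 | 0.96 |
| 0.9 | 0.95 | 0.95 | 1.00 |

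A separate simulation (20,000 trials per value) agreed to within about 0.02 in every cell. At r = 0.6 the equivalent number of pairs is 22/0.84 ≈ 26 (ANCOVA) to 22/0.81 ≈ 27 (common baseline).

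**4. Does the ASD rule repair this?** It was taken to add baseline LDL as a main-effect covariate while baseline stays in the outcome vector. That covariate is constant over a participant's visits, so it cannot move a within-participant contrast. In the two data sets the interaction stayed at −1.428 and −10.543. Only its standard error changed, from 5.95 to 4.17 and from 6.78 to 5.03.

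**5. Dropping the diet main effect alone.** With the pair-only intercept kept, the fitted week-8 effect became the raw mean of D_8 (−12.853 in the first data set). Its variance relative to the change score is V/(2V(1 − r)) = 1/(2(1 − r)): 0.71 at r = 0.3, 1.0 at 0.5, 1.67 at 0.7 and 2.5 at 0.8. With a participant effect added, the common-baseline estimate lay between the two: −5.27, against −1.43 (change) and −12.85 (post-only).

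**6. The planned standard error is a separate matter.** With no participant term, between-participant variance falls into the residual, and the model variance exceeds the true variance of the estimate by a factor 1 + 0.6r/(1 − r). At r = 0.6 that is 1 + 0.6 × 1.5 = 1.9, a standard error about 38% too large (√1.9 ≈ 1.38). The comparison in step 3 therefore uses a correctly specified change-score analysis, not the SAP's Wald test as written.

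**The case against.** A full diet-by-visit model with a free baseline is common and defensible. Under randomisation it is unbiased for the SAP's stated target, the difference in change from baseline. The size of any gain cannot be fixed from the documents, and at high r it is small. All of this stands.

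Four stronger readings are tempting, and none is supported.

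- A reader might infer bias, because chance imbalance and regression to the mean remain in the contrast. They add variance only; baseline is measured before allocation.
- A reader might infer that the planned test is an ordinary change-score test. Only the point estimate matches. The pair-only intercept makes the standard error too large (step 6). In simulations where a paired change-score test has 80% power, the SAP's Wald test has 68% at r = 0.5 and 47% at r = 0.7, while ANCOVA has 88% and 84%. From about r = 0.5 the missing participant term costs more power than the free baseline effect.
- A reader might read (1 + r)/2 as the ANCOVA gain in this trial: 20% at r = 0.6. That is a large-sample figure. At 22 pairs ANCOVA gives about 16%, and nothing by r = 0.9.
- A reader might think that deleting the diet main effect is enough, or that adjustment is free. Step 5 shows that deletion alone can lose precision. ANCOVA on pair differences spends a slope, and drops any pair with a missing value although section 4.2 plans to use all available data.

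**Conclusion.** The point holds as an efficiency weakness in the primary model, repeated in the secondary-outcome models. It is not a validity error. Relative to a correctly specified change-score analysis at 22 pairs, the variance falls by about 29%, 19%, 8% and 5% at r = 0.4, 0.6, 0.8 and 0.9 with a common-baseline model, or by about 26%, 16%, 4% and 0% with ANCOVA.

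These figures rest on complete data, compound symmetry and an assumed r. The existence of the free baseline parameter, and the equality of the interaction estimate with the difference in mean change, follow from the documents and do not depend on r.

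**What to change.** In SAP section 4.2, prespecify for the primary outcome, and likewise for the secondary outcomes:

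- fixed effects for visit and for diet-by-visit at weeks 4 and 8, with no diet main effect, so that both diets share one baseline mean;
- a participant-within-pair random effect in addition to the pair effect, or an equivalent within-person covariance;
- small-sample degrees of freedom for the week-8 and week-4 tests.

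The first two must be adopted together. Prefer this model to ANCOVA on pair differences, which drops incomplete pairs; the latter could be a sensitivity analysis. Baseline LDL can then leave the list of variables that trigger the ASD-based adjustment of the LDL model.

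The cost is a short SAP revision and one extra covariance term (for ANCOVA, one slope degree of freedom). No new data are needed.

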#### 1.2 Study Hypotheses

##### 1.2.1 Primary Hypotheses

- The change in lipids will be different for participants on vegan diet compared to those on omnivorous diet
  - A difference can be seen as early as 4 weeks

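### The primary LDL model has a random intercept for twin pair but nothing for the person, so the standard error of the 8-week contrast is generally mis-stated

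*Combined protocol and SAP*

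**What the plan says.** SAP section 3.1 makes LDL the single primary outcome, with the schedule "Measured at baseline, 4 and 8 weeks". SAP section 4.2 models absolute LDL with "fixed effects for diet and time (baseline as reference) and an interaction effect for diet by time". Its one random term is "a random effect for twin pair, to account for the correlation between identical twins", which the plan explains by adding that a "random intercept allows intercept to vary for each twin pair". The primary test is a Wald test of the 8-week diet-by-time interaction, "at a 5% significance level". If it is significant, the 4-week interaction is tested. On the analysis set the plan says "The primary analysis will include all available data", so all three visits of both twins enter.

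The rest of section 4.2 gives each secondary outcome a similar model and adds covariate-adjusted, exploratory t-test and sensitivity analyses. Nowhere does it name a participant effect, a nested effect or a residual covariance over visits.

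**The concern.** There are two layers of clustering: twins within a pair, and three visits within a person. The model represents only the first. Stable differences between the two twins of a pair then fall into the residual, although they cancel from each person's change from baseline, and the tested interaction is a difference of such changes. The residual that the model uses is therefore not the variance that governs the contrast.

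At stake are the primary confidence interval and p-value. So is the 4-week test, which is reached only through the 8-week result, and so are the secondary outcomes that copy the model. The trial is small and the documents contain no power calculation, so a mis-stated standard error matters.

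**Working it through.** **Inputs from the documents.** Three visits per person (SAP 3.1); one vegan and one omnivore twin per pair (protocol, Randomization); pair intercept only (SAP 4.2); 5% level (SAP 4.2), taken as two-sided because the hypothesis in SAP 1.2.1 is non-directional: "The change in lipids will be different for participants on vegan diet compared to those on omnivorous diet". The SAP has 22 pairs and the protocol 24; the ratios below do not depend on which is used.

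**Assumed, because the documents give none.** LDL SD 30 mg/dL; within-person correlations r04, r48 and r08 between visits; a constant co-twin correlation c. There is no sample size or power figure in the plan to reproduce.

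**True variance.** With total variance scaled to 1 and complete data, the 8-week interaction estimate from n pairs has variance 4(1 − r08)/n. The constant co-twin covariance cancels.

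**Variance the model uses.** After the pair mean is removed, each pair has 5 within-pair degrees of freedom. The sum of squares per pair has expectation 6 − (6 + 4R + 18c)/6, where R = r04 + r48 + r08. Dividing by 5, the residual variance tends to 1 − (2/15)R − 0.6c, and the model reports 4 times this over n.

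**Case A: equal correlation r at all lags.** The residual variance becomes (1 − r) + 0.6(r − c), so

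SE ratio (model/true) = sqrt(1 + 0.6(r − c)/(1 − r)).

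Actual type I error is 2[1 − Φ(1.96 × ratio)]. An effect with 80% power under the correct standard error has power Φ(2.80 − 1.96 × ratio).

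| r | c | SE ratio | Type I error | 80% power becomes |
|---|---|---|---|---|
| 0.7 | 0.7 | 1.00 | 5.0% | 80% |
| 0.8 | 0.7 | 1.14 | 2.5% | 71% |
| 0.8 | 0.5 | 1.38 | 0.7% | 54% |
| 0.9 | 0.3 | 2.14 | below 0.01% | 8% |

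For r = 0.8, c = 0.5 and 22 pairs, the true SE is 30 × sqrt(4 × 0.2/22) = 5.72 mg/dL and the model SE is 30 × sqrt(4 × 0.38/22) = 7.89 mg/dL. Simulations of this case agree. In 1,000 trials the mean model SE was 7.84 against an empirical 5.75. Across the simulations run, type I error was 0.7-0.9% and power 54-56%. Two runs of 20,000 trials with a participant intercept added gave 4.8% and 5.1% type I error, and 80% power.

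**Case B: correlation decays with lag.**

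- r04 = r48 = 0.8, r08 = 0.64, c = 0.5: model 1 − (2/15)(2.24) − 0.30 = 0.401; true 0.36; ratio sqrt(0.401/0.36) = 1.06.
- Same r, c = 0.6: model 0.341; true 0.36; ratio 0.97.
- r04 = r48 = 0.7, r08 = 0.49, c = 0.5: model 1 − (2/15)(1.89) − 0.30 = 0.448; true 0.51; ratio 0.94. Type I error is 2[1 − Φ(1.96 × 0.937)] = 6.6%.

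The model applies one residual variance to both contrasts, so the 4-week test can be further out than the 8-week test. In the first decay example its true variance uses 1 − r04 = 0.2, and the ratio is sqrt(0.401/0.2) = 1.42.

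**Missing visits.** A scenario with no true effect let participants with week-4 LDL above 125 mg/dL miss week 8 with probability 0.6. Applied to the vegan arm only, the pair-only model was biased by −1.7 mg/dL (Monte Carlo SE 0.11), against −0.05 with a participant term. With the same rule in both arms, the pair-only bias was −0.1 to +0.25 (Monte Carlo SE 0.17), which cannot be told from zero.

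**The case against.** **The error is on the safe side.** A reader might infer from Case A that the primary test is simply too conservative, by something like 38%. The documents do not support this. They give no correlations. Food is provided for the first four weeks and self-prepared for the last four, so equal correlation across lags cannot be taken for granted. Under plausible decay the error nearly vanishes or reverses. These are also identical twins, so a high c, which shrinks the error, is plausible. What stands is that the standard error is right only by coincidence. Where it is too wide, a trial of this size loses power that it needs.

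**The estimate is biased.** A reader might also infer that using all available data biases the result whenever dropout depends on a person's own earlier LDL. With complete data the estimate is unaffected. Material bias appeared only when dropout differed by arm, and the documents give no dropout rate. With missing visits the weighting of the observed values is still wrong.

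**The plan relies on a large-sample z test.** The SAP says only that a Wald test is used, and a Wald t is compatible with that. Choosing small-sample degrees of freedom belongs to the remedy and is not a contradiction in the plan.

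**The t-tests cover it.** They are labelled exploratory and do not replace the primary model. Under Case A with complete data, both t-tests on change scores have true variance 4(1 − r)/n. The primary analysis would then be more conservative than the two-sample test that the SAP itself describes as conservative.

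**Conclusion.** The concern holds. As written, the model gives a generally mis-stated standard error, confidence interval and p-value for the primary 8-week contrast. The fault passes to the 4-week gate and to the secondary-outcome models, where its size and direction depend on each outcome's own correlations.

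The size is assumption-based. With equal correlation at all lags and r above c, the standard error is too wide, with ratios from 1.00 (r = c = 0.7) to 2.14 (r = 0.9, c = 0.3). With correlation falling over time, the ratios in the examples were 0.94 to 1.06. That the standard error is mis-specified is certain from the text. The direction is probably too wide if correlation is roughly constant over visits, but it is not established. Because the fault lies in the primary inference and the correction is nearly free, it should be made before the analysis is run.

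**What to change.** In SAP section 4.2, keep the random effect for twin pair and add the correlation within a person, preferably as an unstructured covariance over the three visits within participant. If that does not converge, use a random intercept for participant nested in pair with robust standard errors clustered on pair. The robust step is needed because a participant intercept alone understates the standard error under lag decay. In the first decay example its residual variance is 1 − 2.24/3 = 0.253 against a true 0.36, a ratio of sqrt(0.253/0.36) = 0.84.

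State that the Wald test uses small-sample degrees of freedom (Kenward-Roger or Satterthwaite), and apply the same model to the secondary outcomes. Within-pair differences are not an equivalent replacement: when one twin misses a visit they discard the co-twin's value, which conflicts with using all available data.

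The cost is one or two sentences in the SAP, a few more covariance parameters to estimate from a small trial, and no new data.

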## 8. Participant Population

- a) State the following: (i) the number of participants expected to be enrolled at Stanford-affiliated site(s); (ii) the total number of participants expected to enroll at all sites; (iii) the type of participants (i.e. students, patients with certain cancer, patients with certain cardiac condition) and the reasons for using such participants.

(i) 48 individuals, 24 pairs of twins

**Title :** The Twins Nutrition Study (TwiNS): Vegan vs. Omnivore

**Approval Period:** 06/14/2022 - 12/31/2999

(ii) Healthy adult population

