## Activity Log:

### 1. Study Overview

Background/Introduction: A vegan diet has been promoted as having a much lower environmental impact, but there is some controversy about the health effects of following a vegan diet. Some believe that this plant-based diet can help prevent many of the chronic diseases that affect us, such as heart disease, cancer, and Alzheimer's disease and would also help in managing body weight. Others claim that the vegan diet does not provide all the required nutrients, such as adequate amounts of protein, vitamin B12 and the minerals iron and calcium, and thus it would not promote optimal health. This study is designed to investigate the health impact of a vegan diet compared to an omnivorous diet. We plan to study these diets in twins, where one twin follows a vegan diet and the other twin follows an omnivorous diet, thus we control for genetic differences that might impact the effect of the diet.

Twenty-two pairs of identical twins will be randomized so that one twin will follow the vegan diet, and the other twin will follow the omnivorous diet for 8 weeks. Participants will receive pre-made meals delivered to their home for the first 4 weeks. They will be responsible for their own meals the last 4 weeks. Participants will have 3 in-person clinic visits (baseline, 4 weeks, and 8 weeks), as well as provide stool and micro-samples of blood from home. Changes in food patterns and behaviors and dietary intake assessment will be addressed using multiple tools employed successfully over dozens of studies by the Stanford Nutrition Studies Group.

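### The imbalance-triggered adjusted analysis has no stated form; read as a baseline main effect with complete data, it cannot correct the week-8 diet effect for imbalance, and its trigger responds to chance

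*Combined protocol and SAP*

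**What the plan says.** The primary model (SAP section 4.2) takes LDL at baseline, week 4 and week 8 as the outcome. Its terms "include fixed effects for diet and time (baseline as reference) and an interaction effect for diet by time", plus a random intercept for the twin pair. No participant-level effect is named. The analysis uses every available observation, so incomplete records stay in. The test is a Wald test of the week-8 interaction term "at a 5% significance level".

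Among the secondary analyses, the SAP says that "if any demographic, clinical, or process variables display more than small differences between arms", judged by an ASD above 0.2 in Table 1, the primary model is refitted with adjustment for those variables. It does not say whether a covariate enters as a main effect, by visit, or as a time-varying value, and it sets no limit on how many may enter.

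The clinical variables in Table 1 (section 4.1) are "LDL-C, HDL-C, triglycerides, fasting insulin, fasting glucose, TMAO, weight, serum B12". LDL-C is among them, with no exception for its being the outcome. Table 1 also lists demographic variables and process variables (calorie and macronutrient intake); the process variables also serve as adherence measures.

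On allocation, the protocol says "One of the individuals in each pair of twins will be randomized to a vegan diet, and the other will be randomized to an omnivore" (that is, the comparison arm). The SAP overview gives the size as "Twenty-two pairs of identical twins will be randomized so that one twin will follow the vegan diet"; protocol section 8 gives "48 individuals, 24 pairs of twins".

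**The concern.** An adjusted analysis prompted by baseline imbalance should show whether the imbalance could explain the diet effect. That requires the covariate to be able to act on the quantity being tested, which here is the difference in change from baseline. A baseline covariate entered as a main effect shifts all three of a person's visits equally, so it drops out of change. An unchanged estimate would then be read as reassurance although the model could not have shown anything else.

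Two further features matter. Between twins randomised within pairs, a baseline difference is chance, so the covariate set is chosen by noise. And because the form is open, analysts would choose among versions that give different answers after seeing the data.

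**Working it through.** The plan states no SD, twin correlation, dropout rate or power figure, so there is nothing to reproduce. Inputs from the documents: 22 pairs (SAP), 1:1 within pair, three visits, a pair intercept only, the 0.2 threshold, and eight clinical variables. Everything else below is assumed.

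**1. Complete data, covariate as a main effect.** Each person has all three visits, so the week-8 interaction estimate is

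(mean LDL, vegan, week 8 − baseline) − (mean LDL, omnivore, week 8 − baseline).

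A time-constant covariate x with slope b adds b·x to a person's week-8 value and the same b·x to the baseline value. It cancels in that person's change, whatever b is and however unequal x is between arms. In 300 simulated 22-pair trials fitted by REML, the largest difference between adjusted and unadjusted estimates was 1.7e-12 mg/dL, for a generic covariate and for baseline LDL alike.

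**2. Why the standard error still moves.** Assume pair SD 20, person SD 15 and residual SD 10 mg/dL. With only a pair intercept, person variance falls into the residual:

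- between twins within pair: 3 × 15² + 10² = 775, on 21 df
- within person: 10² = 100, on 84 df
- pooled: (21 × 775 + 84 × 100) / 105 = 235

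The estimate is a contrast of four cell means of 22 people, so:

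- model SE = √(4 × 235 / 22) = 6.5
- true SE = √(4 × 100 / 22) = 4.3

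The simulation gave mean model SEs of 6.45 unadjusted, 5.29 with a generic covariate and 4.47 with baseline LDL. In one simulated trial the estimate stayed at −9.487 while p went from 0.153 to 0.059 to 0.014.

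**3. Dropout after baseline, same assumed SDs.** The main-effect estimate then moves:

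| Loss per person | Generic covariate: mean (max) shift, mg/dL | Baseline LDL: mean (max) shift, mg/dL |
|---|---|---|
| 5% | 0.67 (3.5) | 0.90 (4.8) |
| 10% | 1.07 (7.8) | 1.32 (9.9) |

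Is this a correction for imbalance? In a further simulation (1,000 trials per setting, fixed variances, a covariate assumed to affect change), the correlation between baseline imbalance and the shift in the estimate was:

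| Dropout | Main effect | Covariate by visit |
|---|---|---|
| 0% | no shift | −0.90 |
| 5% | 0.04 | −0.72 |
| 10% | 0.03 | −0.65 |

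The by-visit form responds to the imbalance; the main effect does not.

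**4. Other forms, complete data.** Covariate by visit moved the estimate by 0.40 mg/dL on average (generic covariate) and 0.63 (baseline LDL), at most about 4. A time-varying covariate that diet itself changes moved the mean estimate from −10.05 to −3.38.

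**5. How often the trigger fires by chance.** For a person-level variable with twin correlation ρ:

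SE(ASD) = √(2(1 − ρ)/22), and P = 2[1 − Φ(0.2/SE)].

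For eight independent variables, P(at least one) = 1 − (1 − P)⁸.

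| ρ (assumed) | SE | P, one variable | P, at least one of eight |
|---|---|---|---|
| 0 | 0.302 | 51% | 99.7% |
| 0.5 | 0.213 | 35% | 97% |
| 0.7 | 0.165 | 23% | 87% |
| 0.8 | 0.135 | 14% | 70% |
| 0.9 | 0.095 | 4% | 25% |

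If the eight variables correlate at 0.5 with one another, the last column falls to 92% at ρ = 0.5 and 76% at ρ = 0.7. With 24 pairs the one-variable column becomes 49%, 33%, 21%, 12% and 3%. In identical pairs age and sex do not differ, so they cannot trigger.

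**The case against.** The SAP never says main effect, and it keeps incomplete records. A reader might infer that the adjusted estimate is bound to equal the unadjusted one. The documents do not support that: the identity needs both a main effect and complete data, and other forms or modest dropout move the estimate. This stands, and the point is limited accordingly.

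A reader might also infer that the adjusted analysis would manufacture significance, since p can fall while the estimate stays put, or that baseline LDL on both sides of the model does damage. Neither is shown. In 2,000 simulated null trials with the SDs above and complete data, the unadjusted model had a type I error of 0.3%; with baseline LDL added it was 4.2%. Two other sets of SDs gave 0.7% and 3.3% unadjusted, against 4.6% and 5.3% adjusted. The smaller SE is nearer the true one. The large unadjusted SE comes from the missing participant effect, a separate matter. Baseline LDL as both covariate and outcome is redundant, not demonstrably harmful.

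The trigger rates depend on a twin correlation that the documents do not give, and zero is implausible for identical twins. At 0.9 the trigger is rare for any one variable. The age and sex remark assumes identical twins; the SAP overview says so, but the inclusion criteria ask only for twins. Finally, the rule and threshold are written in advance, and the primary test does not use them. All of this stands. It narrows the point but does not supply a form of adjustment.

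**Conclusion.** The concern holds in limited form. The adjustment is under-specified. In its ordinary reading and with complete data, it cannot correct the week-8 diet effect for baseline imbalance; with dropout the estimate moves, but not in step with the imbalance. The invariance is algebra and needs no assumed values. The SE, dropout and type I error figures rest on assumed variances and are illustrations.

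The trigger is driven by chance: 14% to 35% per person-level variable for twin correlations of 0.8 to 0.5, and 4% at 0.9. The any-of-eight figures are upper-end values because they assume independence. The 22-versus-24-pair discrepancy does not alter the conclusion.

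This is a secondary analysis of the primary outcome. It should be corrected, but the primary estimate and test do not depend on it.

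**What to change.** Replace the ASD trigger in section 4.2 with one pre-specified adjusted analysis:

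- Handle baseline LDL through a baseline-constrained model, or an ANCOVA with week-4 and week-8 LDL as outcomes. State that baseline LDL is not added as a covariate to a model in which it is also an outcome row.
- Name any other baseline covariates now (baseline weight, for example) and enter each with a covariate-by-visit interaction, so that it can act on change.
- For process variables, use baseline values only; later values are affected by the diet.
- Keep the ASDs in Table 1 as description.

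The cost is SAP wording and two or three degrees of freedom per covariate. No new data are needed. The covariate list should be short, given 22 pairs.

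If the trigger is kept, the SAP should at least state the form of adjustment, exempt LDL-C, and say that an unchanged estimate from a main-effect model is no evidence that imbalance was harmless.
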